In June 2020, a tender was put out requesting submissions from suitable community service organisations across Victoria who deliver family services to vulnerable families. Seventeen tenders were released to deliver the program across sites in both urban and regional settings. The goal of the Response was stated as being “strong families-with children who are safe, healthy, resilient and thriving; and parents who are supported to create a safe and nurturing home environment” [15]. The program seeks to provide intensive support to families where the children are at significant risk of being removed and placed in OOHC, or to enable the reunification of removed children in a timely manner. Referrals into the program are made via Child Protection, yet participation is voluntary. The FPR model is premised on the assumption that early, targeted and intensive support will permanently change the trajectory of vulnerable families away from the child protection (CP) system and towards the self-management of needs. OOHC placement often has adverse impacts on the child and family, and is extremely costly [16]. Hence, from a social, emotional and economic perspective, it is much better if families are supported and strengthened to ensure children can stay at home, safely. Table S1 outlines the government-led, individual core components of the Victorian FPR Response. Many are unique compared to other intensive family services by, for example, targeting adolescents, having a focus on implementation science (i.e., exploring *how* the program is being delivered), significant brokerage (i.e., funding to be used to purchase necessities for the family, such as groceries, housing appliances, contribute to rent, medication etc) and a new role within child protection called a Navigator. The Navigator is a government position that has been established within child protection to ensure that coordinated, targeted, appropriate, and culturally safe referrals are made into the FPR program. Rather than being prescriptive in program design, the Victorian government allowed all community service organisations to propose their own version of the FPR Response (within some broad parameters), with the view that consistency will be embedded through the government’s delivery of training and coaching to common practice elements (i.e., core components of program delivery) [17]. MacKillop Family Services was awarded nine areas of Victoria (six urban and three regional) to deliver the program.

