The MacKillop key worker/practitioner engages with the family intensively, defined as a home visit for at least one hour, three times a week, or less visits and regular phone contact plus other activities as required. The timing of these visits is flexible to accommodate the needs of families. Funding is provided to allow for 200 hours of work with an additional 40 hours of step-down towards closure. It is expected that families will engage with the program for approximately six months, but this could last for up to a year. The most practical caseload per full time practitioner is four families, however workers may hold up to six families, albeit at a decreased intensity and with less fidelity to the model. In general, workers focus on reducing stressors and barriers to health and family functioning, such as housing, and offer referrals to specialist services if needed. Workers also focus on the interactions within the family and strengthen core life skills.

For families who are subject to an unborn report (reported to CP while pregnant) or with children aged 0–9, workers use evidence informed methods that focus on parenting skills (i.e., sleep settling, developing routines, responding to cues, use of consequences etc), parent–child attachment, and capacity to effectively respond during a crisis, such as those from the newborn behavioural observation method [20] or circle of security program [21]. These methods support families to meet their goals and mitigate risk. Specifically, the brokerage is a crucial component of the program that helps to fund items that meet families’ immediate or essential needs (i.e., groceries, rent), or can support families to achieve their goals (i.e., fund mental health or substance use counselling). As participation is voluntary and no specific incentives are provided, the brokerage may often be viewed by families as an incentive to engage in the program.

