The program is also designed to support families to link into the community and its services to build independence, self-sufficiency, and a social network. Multi-disciplinary teams forged through partnerships with other agencies enhances the direct engagement of families with experts in parenting, drug and alcohol services, as well as regional care. Once families are better placed to meet the challenges they face and preferably with achieved goals, MacKillop will close the connection, but not before they provide the families with referrals to other programs or services if needed. For some families with young children, and where agreed to by the CP Navigator, an additional episode of care (240 h) will be provided to ensure that the family’s capacity is sufficient to keep children safe and thrive.

Families in metropolitan areas with young people aged 10–17 years engage with the evidence based Multi-Systemic Therapy Psychiatric (MST-Psych) program [22,23] where they see a trained MST-Psych MacKillop worker (termed family therapist) for at least one hour, three times a week. Full time family therapists are expected to hold up to four families and be available after hours where necessary. Family therapists adopt a systems approach by working closely with the child as well as the systems in which they live, e.g., caregiver, broader family members, home environment, school, peers, and community. They implement a range of evidence-based interventions, such as behavioural therapy, parent management training, cognitive behavioural therapy, and family therapy to meet the treatment goals within each system before closure. The regional MacKillop FPR programs also work with families of this age group, however they do not deliver an approved MST-Psych program, rather, they offer a service informed by this expertise.

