### 2.2. Study Design

This study aims to investigate the effectiveness and implementation of the FPR concurrently. To do so, this study adopts a mixed-methods study design involving a longitudinal single group pre-post study design combined with qualitative components. Given that participants are at high risk of child removal, it is not possible to include a control group, and a waitlist or similar group are also not viable. Other alternative study types are also not suited (for example, interrupted time series [24], because we cannot track participants for extended and lengthy periods of time). That is, given that the program’s duration is brief (200 h), highly intensive, and has a unique mix of outcome measures, any possibility for a matched control group regardless of prospective or retrospective data collection is prohibited. For these reasons, a quasi-experimental pre-post study design is being used to evaluate the effectiveness of MacKillop’s FPR program, acknowledging there are limitations to this approach. A multi-methods approach to data collection is being utilised, including focus groups, interviews, surveys, assessment questionnaires, and document analysis. Information from parents is being obtained only from those who provide consent. The study sites include all nine regions across Victoria, Australia, where MacKillop delivers the FPR.

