### 2.3. Participants

There are two participant groups in this study: parents and MacKillop Family Services staff.

Parents: Parents either have children (0–17 years of age) who are vulnerable to removal from the home due to a child protection assessment of risk, have children already in OOHC, or are pregnant and have had ‘unborn’ reports to child protection. These parents may have multiple factors that are contributing to their risk profile including recent family violence, drug or alcohol misuse, fragile mental health, court orders and justice involvement among others. Parents can vary in age and may be adolescent parents or those who are currently living in a care arrangement (foster, kinship, or residential OOHC). Sample size calculations have been conducted using G*Power based on the NCFAS as this measure goes across most efficacy outcomes. For an analysis of variance test with the alpha set at 0.005, correlations between repeated measures set at 0.50 and power of 0.95, a total sample of 98 families will be required. To allow for a 25% rate of non-completion, at least 123 families will be recruited. During the study period, it is expected that up to 1100 families will engage in MacKillop’s FPR program. Based on similar research, we expect a high number of families to consent to participate in the study [25], therefore, it is expected that this sample size requirement will be met by the end of the study period.

MacKillop Family Services Staff: MacKillop directors, managers, team leaders and practitioners involved in the delivery of the FPR program are eligible to participate in interviews or focus groups about their experiences of implementing the program. Only staff who consent will take part in the research evaluation.

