#### 3.1.4. FPR Effectiveness in Reducing Reports to Child Protection and Subsequent Placement into OOHC

To understand if the MacKillop Family Services FPR has been successful at reducing family involvement with child protection and preventing children from entering/re-entering OOHC, three types of linked data from the government are being sourced, subject to approval: (1) reports made to child first, or other child protection organisations who use the Client Relationship Information System (CRIS) system, about FPR children and parents in the six months before participating in the FPR, the six months during and then six months after program closure; (2) number of times children have been in OOHC in the 12 months post FPR participation; (3) time to reunification after removal; or (4) time to removal/re-removal.

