## 4. Analytical Considerations

The primary quantitative outcome of this study is to examine the degree to which there are improvements in psychosocial outcomes among families who engage in the program. All completed questionnaires will be de-identified by a specific data aggregation worker who will assign a unique ID code (e.g., FPR003) to each family so that their data remain anonymous to the research team. Descriptive statistics will be calculated based on administrative and demographic data sourced from the referral form. Main caregiver complexity will be determined using the ACEs survey and the number of ACEs will be calculated. A series of paired sample t-tests (repeated measures) will be used to compare participants’ mean differences on the measures at the beginning and end of the program. Analysis of Variance will be employed to review the number of reports before, during and after the program to determine any statistical differences. The number of care episodes and time to reunification will be analysed descriptively. All analyses will be performed using the Statistical Package for the Social Sciences (SPSS) software.

All qualitative data will be analysed using thematic analysis [41]. Data collection and analysis will occur concurrently so that data saturation can be adequately assessed. All audio recordings will be transcribed verbatim and systematically coded. Following in-depth review of the coded data, independent themes will be identified and developed based on recurrent content reflecting the different aspects of program implementation. The process of refining and reviewing themes will be an iterative process until themes are representative of the most pertinent and recurrent aspects of the data.

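### The before/during/after comparison of child-protection reports starts from a window raised by the event that led to referral, so a fall is expected even with no programme effect

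*Protocol article*

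**What the plan says.** Section 3.1.4 plans to use linked government records, subject to approval, to learn whether the programme reduces families' involvement with child protection. Reports are to be counted "in the six months before participating in the FPR, the six months during and then six months after program closure". Section 4 fixes the test: "Analysis of Variance will be employed to review the number of reports before, during and after the program to determine any statistical differences". Section 2.2 explains that no control group is possible and acknowledges, in general terms, that the design has limitations. It does not mention selection on a report or regression to the mean.

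On entry, Section 1.1 says: "Referrals into the program are made via Child Protection, yet participation is voluntary". Section 2.3 gives three routes:

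- parents whose children are "vulnerable to removal from the home due to a child protection assessment of risk";
- parents who "are pregnant and have had ‘unborn’ reports to child protection";
- parents with a child already in out-of-home care.

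On duration, Section 1.2 says: "It is expected that families will engage with the program for approximately six months, but this could last for up to a year". For some families with young children, "an additional episode of care (240 h) will be provided". Table 1 (Readiness and Reach) also expects some families to close early.

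**The concern.** The first window ends at the moment a family is referred, and referral depends on child-protection concern. On the unborn route a report is itself the entry condition. On the at-risk route a recent report is a fair inference. The two later windows carry no such condition. A family with an unchanging report rate will therefore tend to show more reports before than after, simply because of when it was picked, and no comparator removes this.

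The result would be read as the answer to the question Section 3.1.4 sets, whether the programme reduces reports. A significant fall produced by selection would be taken for effectiveness on the only record-based outcome with a planned significance test; care episodes and time to reunification are descriptive.

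A second, separate matter is that fixed six-month windows do not fit programmes of varying length, so it is unclear what the programme window counts.

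**Working it through.** **Inputs.** The article gives no figure for the report analysis, so there is none to reproduce. The 98 families come from the NCFAS sample size calculation (Section 2.3) and are used here only as a plausible number analysed. The report rate and the share of families entering on a report in the last six months are assumptions, shown as ranges. Alpha is taken as 0.05; the 0.005 in Section 2.3 belongs to the NCFAS calculation.

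**Step 1: expected counts with no effect.** Let each family have a constant Poisson rate λ per six months. Conditional on at least one report in the window before entry, the mean of that window is λ / (1 − e^(−λ)); the later windows stay at λ. If a share s is so selected, the mean before is s·λ/(1 − e^(−λ)) + (1 − s)·λ.

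| λ | before, s = 1 | before, s = 0.5 | after | spurious fall, s = 1 | spurious fall, s = 0.5 |
|---|---|---|---|---|---|
| 0.5 | 1.27 | 0.89 | 0.50 | 61% | 44% |
| 1 | 1.58 | 1.29 | 1.00 | 37% | 23% |
| 2 | 2.31 | 2.16 | 2.00 | 14% | 7% |

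**Step 2: the planned test.** Simulated repeated-measures ANOVA over three windows, 98 families, no programme effect, rejection at 0.05:

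| share selected | λ = 0.5 | λ = 1 | λ = 2 |
|---|---|---|---|
| all | 100% | 99.5% | 37% |
| half | 98% | 59% | 14% |
| a quarter | 47% | 16% | 6% |

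Separate runs differ by up to about four percentage points. With rates varying between families (gamma, mean 1, shape 1) and all families selected, the means are 2.00 before and 1.50 after, and the test rejects in 87% of runs.

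**Step 3: a different model of entry.** Add one entry report to the first window for a share q of families, with gamma-distributed rates of mean 1. The expected fall is then q reports per family. Rejection at 0.05 is 5% at q = 0, 11% at 0.10, 40% at 0.25, 94% at 0.50 and 100% at 1. At alpha 0.005 it is still 77% at q = 0.50. The direction is the same under both models.

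**Step 4: programme length alone.** With no entry report, mean rate 1 and lengths spread evenly over 3 to 12 months, the means before/during/after are:

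- fixed six-month windows: 1.00/1.00/1.00, rejection 5%;
- programme window cut at closure: 1.00/0.91/1.00, rejection 7.5%;
- whole programme counted: 1.00/1.25/1.00, rejection 35%.

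Before and after stay equal in all three. Only the middle window moves, according to how it is read. With fixed windows a 12-month programme leaves 12 − 6 = 6 months uncounted, and a 3-month one makes the second and third windows overlap by 6 − 3 = 3 months.

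**Step 5: candidate remedies.** In the model of Step 1 with all families selected, deleting the triggering report leaves 0.27/0.58/1.31 before against 0.50/1.00/2.00 after, a spurious rise, rejected in roughly 74%, 91% and 96% of runs. Under Step 3 the same deletion would be right, so its effect depends on a mechanism nobody knows. Using months 7-12 before connection as the comparison period brings rejection back to about 5%. Given a family's stable rate, that period is not conditioned on the recent report.

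**The case against.** Much can be said for the plan.

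- *Not every family enters on a recent report.* This stands. Only the unborn route strictly requires a report, and a child already in care implies none in the last six months. The case with all families selected is an upper bound. At a quarter selected and two reports per six months the distortion is negligible (6%).
- *Programme length does not create a fall.* A reader might infer that the mismatch between six-month windows and programmes of up to a year adds to the before-to-after drop. Step 4 shows that it does not. It leaves the programme window ambiguous, and Section 3.1.4 may simply be using the expected six-month duration as shorthand.
- *ANOVA on skewed counts is not the problem.* Without entry selection the test held its level (4-5%) on skewed counts. A count model on the same windows would inherit the same selection bias.
- *Reports are not the only outcome free of staff or parent rating.* Adolescents complete the BSI and, where possible, the SDQ (Sections 3.1.2 and Table 1), and care episodes and times to removal are also linked data.
- *The rejection of interrupted time series is not a contradiction.* A reader might set "because we cannot track participants for extended and lengthy periods of time" against the linkage period. That remark concerns tracking participants; the linkage uses government records that were not yet assured.
- *Reports are not primary, and the claims are modest.* Section 4 makes psychosocial improvement primary, the Discussion promises only some conclusions about potential impact, and the scale-up statement in the Conclusions concerns change from baseline to closure.

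These points limit the size and the severity. None removes the bias in the first window, and the general acknowledgement in Section 2.2 does not tell a reader that a fall is expected from selection.

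**Conclusion.** The concern holds for the first window. As planned, a significant fall in reports from before to after can arise with no programme effect, because for many families the first window is raised by the event that led to referral. With 98 families the false-positive rate at 0.05 runs from about 6% (a quarter selected, rate 2) to about 100% (all selected, rate 0.5). At one report per six months with half selected it is about 59%. These figures assume a stable Poisson rate; neither the rate nor the share is in the article, so the direction is firm and the size is not.

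The undefined programme window is a separate weakness of definition and does not itself cause a before-to-after fall. The documents do not support saying that every family enters on a report, or that ANOVA fails because counts are skewed. This should be fixed, but it does not threaten the primary outcome.

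**What to change.** Change the linkage request while approval is pending, and the analysis paragraph in Section 4:

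1. Request dated reports from at least 12 months before connection. Make months 7-12 before connection the main pre-programme period, and show months 0-6 separately, labelled as affected by selection.
2. Do not simply delete the triggering report, which can bias the other way.
3. For unborn and very young children, count reports at family or parent level or analyse them separately, since an earlier child-level window may not exist.
4. Define the programme period as actual connection to closure and compare rates per month at risk, for example by a Poisson or negative binomial GEE with log time as offset and family as cluster. The offset is needed because period lengths then vary.
5. State that a fall from the 0-6 month window alone is not evidence of effectiveness.

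The cost is a longer data extract, which the data custodian must agree to, and slightly more analysis. No further contact with families is needed. The remedy still assumes that rates were roughly stable over the year before connection; the dated reports would let the team look at this.

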### 4.1. Data Management

All project materials, including data, are stored on a secure password-protected online database. Only the chief investigator from Monash University has access to the data set. All data will be deleted six years following the conclusion of the project. Any adverse events that occur as a result of this project will be reported to the Monash University Human Ethics Committee and managed accordingly. An independent audit will occur annually to ensure appropriate trial conduct is upheld and that the data collected and stored is accurate and confidential. Given this, a data monitoring committee is not necessary.

### 4.2. Dissemination of Findings

The findings will be disseminated to MacKillop Family Services via regular meetings and reports to the organisation throughout the three-year evaluation period. A summary of findings will be shared with participants. It is also intended that the findings of this hybrid effectiveness-implementation evaluation will be disseminated with the public via a series of publications in peer-reviewed journals. The research team from Monash University and key stakeholders involved in the delivery of the program from MacKillop Family Services will be included as authors on such publications, where relevant.

## 5. Discussion

This paper describes the protocol of a hybrid style, implementation and outcomes study using a pre-post design with selected follow-up data and qualitative data. The study will serve two key purposes. First, it will seek to demonstrate the extent to which the Response is effective in improving outcomes for families and children following the program. Whilst this is not a randomised controlled trial, the pre-post design will allow some conclusions to be made about the potential impact of the program on engaged families. In turn, this will develop the Response’s evidence base and provide new knowledge about the implementation of intensive family services more broadly. Second, the findings of this study, particularly the implementation findings, will help inform future iterations of the program. It is intended that key program components, processes, or operational issues may be adapted, refined, or remedied to improve implementation and uptake of the Response. Therefore, the evaluation will help ensure that the program is trialled, tested, and adapted accordingly to effectively meet the complex and unique needs of some of the most vulnerable families in the Victorian community.

